**Comorbidities.** Using ICD 9CM codes we will create indicators of advanced complications of diabetes, limited life expectancy, cardiovascular or ischemic vascular disease, and major medical and mental health conditions that would impact benefit or risk of tight control based upon previously published taxonomies.

**Demographic Variables.** We have developed algorithms to process multiple entries of patient data over time and from a variety of sources to optimize the demographic information available for research. Sources include many years of VA inpatient and outpatient data with multiple fields and Medicare data. Consequently, we have nearly complete and largely confirmed assignments for most variables, including age and sex. Because of limitations in data concerning race/ethnicity, we will not assess this variable.

**2.4.6. Identification of High and Low Performers.** High and low performers will be identified based on changes in facility overtreatment rates pre- and post-initiative (rather than on absolute values). Those with the greatest (high performers) and least reduction (low performers) in overtreatment rates will be selected. To

minimize issues related to regression to the mean, we will focus on facilities that were mid-performing at baseline (2nd and 3rd quartiles). See Fig. 4. Among the middle-performing facilities at baseline, we will select those facilities with the greatest reduction in overtreatment rates (high performers) and those with the least reduction (low performers). We will also select from among the highest performers at baseline who improved at all as well as some low performers at baseline who stayed low. It is impossible to know how many facilities will fall into these categories; but we are anticipating approximately 5-10 in each group (total n~30). Aim 3 does not include hypothesis testing, but is instead looking for identifying patterns of provider and facility characteristics associated with performance status (high vs. low). Our methods of analyses (matrix and qualitative comparative analysis) allow for a small sample size. Performance status will be determined independently of Choosing Wisely participation status; selected sites will likely include those facilities choosing the hypoglycemia initiative alone or both hypoglycemia and low back pain initiatives. If entire VISNs participate

[figure not shown]

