factors may only be causal in the presence of other factors, and when the absence of the outcome has a different causal pathway than simply the absence of factors associated with the outcome (i.e., causal asymmetry). We will define approximately six to eight independent variables for use in the QCA. Selection of these variables will be based on the findings from the matrix analysis and will include those toolkit components and those CFIR constructs

that (1) distinguish between low and high performers (i.e., negative or absent in low sites, positive or present in high sites); (2) were absent or negative in most sites, regardless of performance; and (3) were positive or present in most sites, regardless of performance.

QCA will allow us to determine those constructs whose positive manifestations (rating of 1) are *necessary* for achieving high performance. A construct is considered necessary if it is always positive in high-performing sites. That is, high performance cannot occur in the absence of a positive manifestation of the construct, but its presence does not guarantee high performance. QCA will also determine those constructs or combination of constructs that are *sufficient* for achieving high performance. A construct or combination of constructs is sufficient for high performance if high performance always occurs when the positive manifestation of the construct or combination of positive constructs is present. The presence of a sufficient construct or combination of constructs guarantees high performance when the necessary constructs are present. For example, we may find that a particular toolkit component is necessary, but not sufficient for high performance. Thus, a policy recommendation might be to recommend that all facilities at a minimum implement the necessary component, as without it facilities have no chance of success. We may also find that no components are necessary, but three of the available components are sufficient. Thus, a policy recommendation might be to recommend at least one of the three components, and allow facilities to select from among any of the three sufficient components. For example, among the components likely to be necessary, if not sufficient, are clinical reminders and local audit and feedback.

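### Aim 3 sites are chosen for extreme change, so a component found sufficient in the QCA separates sampled high from low performers; it cannot be said to guarantee high performance

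*Protocol*

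**What the plan says.** Section 2.4.10 (Mixed Methods Analysis) gives the rule: "A construct or combination of constructs is sufficient for high performance if high performance always occurs when the positive manifestation of the construct", or the combination, is present. The next sentence reads: "The presence of a sufficient construct or combination of constructs guarantees high performance when the necessary constructs are present". A hypothetical example follows in which three components prove sufficient: "Thus, a policy recommendation might be to recommend at least one of the three components", with facilities free to pick among them. The end of the section plans the same analyses with low performance as the outcome.

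Section 2.4.6 selects the sites by change in overtreatment rate: "Those with the greatest (high performers) and least reduction (low performers) in overtreatment rates will be selected". To limit regression to the mean, "we will focus on facilities that were mid-performing at baseline", meaning the second and third quartiles. Two groups are added: top baseline performers that improved by any amount, and some poor baseline performers that remained poor. The protocol expects about 5-10 sites per group and about 30 in all.

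The 0/1 ratings used in the QCA come from the interviews. Section 2.4.9 holds these at the highest and lowest performers only, and sections 2.4.9 and 2.5 limit the surveys in the same way. No section plans to rate mid-baseline facilities with intermediate change. Section 2.5 defends QCA as a method but does not discuss this gap.

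**The concern.** Sufficiency is a claim about every facility that has the configuration: all of them must be high performers. A counter-example is a facility that has it without high performance. Selecting on the outcome removes most of the places where one could be found. Among the mid-baseline sites rated, a component looks sufficient once at least one high performer has it and no low performer does, however many average sites share it. This happens even with error-free ratings and no sampling noise.

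The condition about necessary constructs does not cure this, because unrated sites may hold those constructs too. The low-performance analysis has the mirror problem.

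At stake is what Aim 3 may conclude. A component that usually goes with average change could be described to facilities as enough to secure high performance.

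**Working it through.** **The plan's own counts.** About 5 interviews x 30 sites = 150, and 30 respondents x 30 sites = 900 surveys; both match section 2.4.9. Four groups of 5-10 give 20-40 sites, consistent with about 30. The sufficiency rule itself carries no figure to reproduce.

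**How many sites are unrated.** Section 2.4.4 works with 130 facilities, so the two middle baseline quartiles hold about 130/2 = 65.
- 5 per extreme: 65 - 10 = 55 unrated (85%)
- 8 per extreme: 65 - 16 = 49 unrated (75%)
- 10 per extreme: 65 - 20 = 45 unrated (69%)

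**Consistency in the extremes against all 65 sites.** Let nH, nA, nL be the numbers of high, average and low changers, and pH, pA, pL the share of each with the component. The protocol gives no prevalences; those below are assumptions.
- Consistency in the extremes = pH nH / (pH nH + pL nL)
- High performers among all sites with the component = pH nH / (pH nH + pA nA + pL nL)
- High performers among sites without it = (1 - pH) nH / (65 - number with it)
- Chance that the sample shows perfect sufficiency = (1 - pL)^nL x [1 - (1 - pH)^nH]

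Lead case, 50%/25%/0%:
- 8/49/8 sites: 4/(4 + 12.25) = 25% with the component; 4/48.75 = 8% without it
- 10/45/10 sites: 5/(5 + 11.25) = 31% with; 5/48.75 = 10% without
- Consistency in the extremes is 100% in both, and perfect sufficiency is almost certain (1 - 0.5^8 = 99.6%)
- With 5/55/5 sites: 2.5/(2.5 + 13.75) = 15% with; 2.5/48.75 = 5% without

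Other cases, with 8 and then 10 per extreme:

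| pH/pA/pL | Consistency in extremes | Chance of perfect sufficiency | High, with component | High, without |
|---|---|---|---|---|
| 60%/30%/5% | 92%, 92% | 66%, 60% | 4.8/19.9 = 24%, 6/20 = 30% | 3.2/45.1 = 7%, 4/45 = 9% |
| 50%/50%/0% | 100%, 100% | above 99% | 4/28.5 = 14%, 5/27.5 = 18% | 4/36.5 = 11%, 5/37.5 = 13% |

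**The most favourable sample.** Suppose every selected high site and no selected low site has the component. If a share f of the unrated sites also has it, consistency over all 65 is nH / (nH + f nA). For f = 10%, 25%, 50%, 75% this gives 69%, 47%, 31%, 23% with 10 per extreme, and 48%, 27%, 15%, 11% with 5 per extreme.

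**Simulation.** This used 65 sites, 20,000 runs per setting, component prevalence 30% or 50%, and a shift in change of 1 to 2 SD (all assumed). With 10 per extreme, the extremes showed perfect sufficiency in 17-94% of runs, while mean consistency over all sites was 26-47%. With 5 per extreme the figures were 51-98% and 14-25%. With no effect at all, the extremes still showed perfect sufficiency in 0.1-14% of runs across 5 to 10 per extreme.

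**The case against.** **The research questions.** A reader might infer that RQ3.1 and RQ3.2 will be answered wrongly. The protocol does not support that. Both ask which configurations are associated with greater reduction, and Aim 3 compares high with low performers. In the lead case the component is associated with high performance: 25-31% with it against 8-10% without it, around a base rate of 8/65 = 12% to 10/65 = 15%. The contrast of extremes can show this.

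**Sites never seen.** A reader might also infer that no ordinary-change site is ever rated. That is too strong. The two added groups are chosen partly on baseline level and may contain such sites. Those that improved from a good baseline appear to count as high and so cannot be counter-examples, but the poor baseline sites that remained poor could be. The arithmetic above omits both groups. If about 15 low sites were rated (assumption), the 60%/30%/5% case would show perfect sufficiency about 0.95^15 = 46% of the time, not 60-66%. The arithmetic also treats single components, while the plan includes combinations.

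**A built-in ceiling.** High performance is a rank. If only 10 of 65 sites are called high, any component held by more than 10 cannot be sufficient across all 65, however effective it is. This stands, and it limits how the low full-set percentages should be read. It also shows why a guarantee is the wrong language for a rank-based outcome.

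**Stated caution.** Section 2.4 promises cautious causal inference, and sections 2.4.6 and 2.4.10 disclaim formal testing. The policy text is hypothetical, and the specific recommendations also draw on interview memos and site visits. It would be unfair to read the example as a commitment. But none of this qualifies the sufficiency rule or the word 'guarantees'.

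**Conclusion.** The point stands as a limit on what the QCA may conclude. Perfect sufficiency in the selected sites does not show sufficiency across facilities, because about 45-55 of roughly 65 mid-baseline sites cannot act as counter-examples. Neither the guarantee in section 2.4.10 nor its mirror for low performance can be supported.

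The site counts follow from the protocol's figures, taking 130 facilities as the total. The size of the gap rests on assumed prevalences and on the mid-baseline sites alone, so the percentages illustrate the problem and do not predict the result. The direction does not depend on the particular values: any unrated site that has the configuration without high performance lowers consistency below what the sample shows.

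The necessity analysis is less affected, since as defined it needs only the high-performing sites. Aims 1 and 2 are untouched.

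**What to change.** In section 2.4.10, delete the statement that a sufficient configuration guarantees high performance. State that sufficiency means only that the configuration separates the sampled high from the sampled low performers, and say the same for the low-performance analysis. Add that policy for all facilities will not rest on sufficiency alone, and list selection on the outcome among the limitations in section 2.5. This costs wording only.

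Optionally, use some of the 30 or so slots to rate mid-baseline sites with average change, coded as neither high nor low, as a check on sufficiency. With 10 such sites (assumed), the chance that at least one has a component held by a share p of average sites is 1 - (1 - p)^10: 65%, 94% and 99.9% for p = 10%, 25% and 50%. Interview numbers stay the same. The price is fewer sites from the other groups, including the persistently poor performers that inform the analysis of failure, and a hard cut through a continuous change score. That trade-off is for the investigators to weigh; the wording change is needed either way.

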***Semi-Structured Interviews.*** A semi-structured interview guide will be developed consisting of questions designed to obtain input on the organizational and provider factors identified as most important from the surveys. As part of the Specialty Care Evaluation project, we have developed multiple interview guides addressing most of the CFIR constructs. These questions have been used successfully thus far for four different Specialty Care initiatives; for a draft, we have selected potentially relevant questions from these previously developed guides and tailored them for this study (see Appendix). The interviews will also contain questions about which elements of the toolkit have been implemented. Potential respondents (the clinical pharmacy specialist, director of primary care, and primary care providers) will be contacted via an email invitation followed by a phone call. All interviews will be conducted by two research team members, with one conducting the interview (audio-taped) and one taking field notes. Based on our experience with the Evaluation Center and others, we will conduct approximately 5 interviews per facility for the highest and lowest performers (n=150). If saturation is not achieved, we will conduct additional interviews.

***Site Visits.*** Once the analyses have been completed and the key constructs identified (see analysis plan below), we will conduct site visits to the highest performing sites; we will select facilities of various levels of complexity and location. (We have budgeted for 8 visits.) The primary purpose of the site visits will be to obtain detailed information on site-level manifestation of the constructs associated with implementation success. Interviews will be conducted with the clinical pharmacy specialists, primary care providers, and clinical managers. Clinics will be visited and artifacts collected, e.g., education materials, screen shots of CPRS (using test patients) illustrating decision support, clinical reminders, and lab comments on A1c. Site visits will require 2 days by a 2-person team. We will use methods adapted from prior work conducted by colleagues with the Center for Organization, Leadership, and Management Research (COLMR).

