In addition to conducting analyses of necessity and sufficiency for the outcome of being a high performer, we will conduct similar analyses with the outcome of being a low performing facility. This is required because the causal recipe to failure can be as useful within a learning organization as that of success. [name] will provide expert consultation on the use of QCA. She has used this approach previously in determining best practices in VHA's MOVE! Weight Management Program for Veterans and is PI on a current Agency for Healthcare Research and Quality-funded methods grant to assess the feasibility of using QCA to explain heterogeneity within systematic reviews of complex interventions. Once the important constructs and combinations of constructs have been identified from our analyses, we will go back to the summary memos from our interviews to obtain additional information on the specific practices at sites in which these constructs were positively manifested. In addition, data from the visits to high performing sites will be analyzed descriptively for identifying best practices, and the findings from these analyses will then become the basis of our specific recommendations for improving dissemination of the Choosing Wisely Initiative.

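### The step that names specific best practices looks at high performers only, so a practice equally common at low performers can be recommended

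*Protocol*

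**What the plan says.** The Site Visits paragraph of protocol section 2.4.9 states: "we will conduct site visits to the highest performing sites; we will select facilities of various levels of complexity and location". It adds "We have budgeted for 8 visits". The visits come after the comparative analyses, and their aim is given as follows: "The primary purpose of the site visits will be to obtain detailed information on site-level manifestation of the constructs associated with implementation success". Teams are to collect practice-level material such as education handouts, decision-support screen shots, reminders and laboratory comments on A1c.

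The end of section 2.4.10 then says that "data from the visits to high performing sites will be analyzed descriptively for identifying best practices", and that "the findings from these analyses will then become the basis of our specific recommendations for improving dissemination of the Choosing Wisely Initiative".

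Low performers do enter earlier in the sequence. Section 2.4.9 plans interviews in both groups ("we will conduct approximately 5 interviews per facility for the highest and lowest performers (n=150"), with questions about which toolkit elements were put in place. Section 2.4.10 codes toolkit components and CFIR constructs 0 or 1 for each site, relates the ratings to performance in a matrix, and runs QCA for high performance and again for low performance.

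**The concern.** Performance does not vary among the visited sites. A description of what those sites do cannot, by itself, separate a practice linked to falling overtreatment rates from one that is ordinary at every facility, including those that got worse. Section 2.4.10 states no comparison with low performers for this step, although this step turns broad constructs into the concrete practices to be passed on.

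The specific recommendations are at stake. Table 1 in section 3.0 lists executive briefs to policy offices, network directors and national leadership. If a common but inert practice is labelled best, facilities may spend effort on something that does not distinguish success from failure.

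**Working it through.** **Step 1. Does the earlier high-low contrast already cover specific practices?** Section 2.4.10, read stage by stage:

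| Stage | Sites used | What is compared | Does it remove items common to both groups? |
|---|---|---|---|
| Matrix analysis | High and low | Toolkit components, CFIR constructs | It shows them, but variable-selection criterion (3) keeps items present in most sites whatever their performance |
| QCA necessity | High sites (for high performance) | Same | No: an item present at every site qualifies as necessary |
| QCA for low performance | Low sites | Same | Could expose such an item, but no rule compares the two results |
| Return to interview memos | Sites with a positive construct | Specific practices | No: sites are chosen by construct, and no high-low comparison is stated |
| Site visits | Highest performers | Specific practices | No: no low site is visited |

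The contrast therefore works on components and constructs. It does not reach the particular form of a practice first recorded at a visit, and its screen lets common items through.

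**Step 2. How often could a non-discriminating practice qualify?** The plan gives no error rate or cut-off for this step, so there is no stated figure to reproduce. The interview count is consistent: 5 per site × about 30 sites = 150.

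Inputs:
- n = 8 visits (section 2.4.9).
- p = share of sites with the practice, the same at high and low performers. Assumption, range 0.3 to 0.9.
- r = number of visited sites at which the practice must be seen to be called best. Assumption: 5, 6 or 8.
- Sites are treated as independent.

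Formula: P(X ≥ r) = Σ from x = r to 8 of C(8,x) p^x (1−p)^(8−x).

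Worked case, p = 0.8:
- x = 5: 56 × 0.32768 × 0.008 = 0.147
- x = 6: 28 × 0.26214 × 0.04 = 0.294
- x = 7: 8 × 0.20972 × 0.2 = 0.336
- x = 8: 0.8^8 = 0.168

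The sums are 0.944 for r = 5, 0.797 for r = 6 and 0.168 for r = 8.

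| p | r = 5 | r = 6 | r = 8 |
|---|---|---|---|
| 0.3 | 0.06 | 0.01 | 0.00 |
| 0.5 | 0.36 | 0.15 | 0.00 |
| 0.6 | 0.59 | 0.32 | 0.02 |
| 0.7 | 0.81 | 0.55 | 0.06 |
| 0.8 | 0.94 | 0.80 | 0.17 |
| 0.9 | 0.995 | 0.96 | 0.43 |

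The chance exceeds one half from p of about 0.6 at r = 5 and from about 0.7 at r = 6. At r = 8 it does so only near p = 0.95, where it is 0.66.

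**Step 3. What would a comparison add?** Assume that 8 low performers can be checked for the same practice; section 2.4.6 expects roughly 5 to 10 sites per group. Flag a practice only if it is seen in at least 5 of 8 high and at most 4 of 8 low sites. The chance is P(X ≥ 5) × [1 − P(X ≥ 5)]. At p = 0.8 this is 0.944 × 0.056 = 0.05, against 0.94 without the comparison. At p = 0.5 the gain is smaller, from 0.36 to 0.23. If the practice must instead be seen in at least 5 of 8 high sites and in at least 4 more high than low sites, the chance is at most 0.04 at every p tried.

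**The case against.** The strongest reply is that the visits are the last, explanatory step of a sequence in which performance does vary. What the teams look for is set by interviews, matrix analysis and QCA across about 30 high and low sites. Criterion (1) for choosing QCA variables is that they separate low from high performers. Clinical reminders and local audit and feedback are named as components, and components are coded for every site, so some specific practices do get a contrast. The wording on what the recommendations rest on uses a plural that may include the QCA. Studying positive deviants is a stated purpose (sections 2.4.6 and 2.4.8 treat Aim 3 as separate from the modelled hypotheses), and Aim 3 disclaims hypothesis testing.

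Most of this stands, and it rules out three stronger readings that a reader might infer:
- *That presence at a high performer is the only input to the recommendations.* The earlier contrast contradicts this.
- *That practices which differ between high and low sites are never singled out.* Criterion (1) and the low-performance QCA can do so for components and constructs.
- *That a common practice will usually be recommended.* The plan describes a qualitative step without a counting rule. The probabilities above depend on an assumed prevalence and cut-off, and under the 5-of-8 rule the chance is only 0.36 at 50% prevalence.

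The reply does not supply a comparison for practices identified at visits. Whether laboratory comments or education materials are themselves coded components cannot be judged, because the toolkit appendix is not in the document at hand.

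**Conclusion.** The point holds in a limited form. The final step that identifies best practices is confined to high performers, and the earlier screen does not reliably remove items shared by both groups. A specific practice equally common at low performers can be labelled best and recommended, and this is likely if it is widespread.

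The size is illustrative. At 80% prevalence in both groups the chance runs from 0.17 (all 8 sites required) through 0.80 (6 of 8) to 0.94 (5 of 8). It is low for practices found at half the sites or fewer unless the cut-off is lenient. These figures assume equal prevalence in the two groups, independent sites and a counting rule that the plan does not state. The weakness concerns the specific recommendations from Aim 3. It does not affect the Aim 1 and Aim 2 models.

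**What to change.** Keep the 8 visits as planned and add a rule to section 2.4.10. Before any practice identified at a visit is called a best practice, check it against the interview memos and 0/1 component ratings already planned for the low performers. Then report it in one of three ways:
- more frequent at high than at low performers: best practice, with the counts in each group;
- similar frequency in both groups: common practice;
- not covered by the low-performer interviews: observed at high performers only, with no comparison available.

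The frequency difference that counts as higher should be written down before the visit data are reviewed, because an undefined margin would leave the same ambiguity.

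The cost is some extra analysis time, with no new visits or staff. The limit is that interviews precede the visits, so the memos may not cover every practice first seen on site. Moving some visits to low performers is a possible alternative, but it is a debatable trade-off. A split such as 5 high and 3 low would give a thin contrast and fewer high performers seen in person, so it is not needed for this repair.
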